**2. STUDY OUTCOMES**

**2.1 Primary Outcome**

The primary outcome of this study is time to treatment failure

Treatment failure is defined as: in addition to other AEDs due to lack of efficacy; discontinuation of SRVPA or topiramate due to lack of efficacy, intolerable adverse events, lack of efficacy combined with intolerable adverse events, poor compliance, patients’ financial hardship, or a plan of pregnancy. A patient with poor compliance was defined as having discontinued SRVPA or topiramate treatment by his or her own volition.

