**2.2 Secondary Outcomes**

Secondary clinical outcomes are the time to first seizure, the time from SRVAP or topiramate treatment to achieve 12-month remission of seizures, the time to 24-month remission of seizures. The incidence of clinically important adverse events and the incidence of intolerable adverse events directly leading to treatment failure were also analysed

Patients achieve 12-month (or 24-month) remission of seizures are defined as patients without any type of seizure for at least 12 months (or 24 months).

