**3. METHODOLOGY**

**3.1 Study Design**

Observational cohort design is to assess the effectiveness of SRVPA and TPM in Chinese epileptic patients.

For the patients with a definite diagnosis of epilepsy, an appropriate AED was chosen by the clinicians, taking into consideration the efficacy and adverse events of the available AEDs, the clinical characteristics and the economic status of the patient. The patients also had the right to refuse the clinicians’ prescriptions and could discuss the drugs with the clinicians to decide which AED would be chosen.

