**3.5 Procedures**

The information recorded during the first visit included patient demographics, information about previous antiepileptic treatment, history of febrile seizures, birth traumas, epilepsy in first-degree family members, and neurological diseases (e.g., stroke, head injury, cortical development disorder, or intracerebral infection). A general physical examination and a neurological examination were performed. Laboratory examinations were carried out. Electrocardiogram (ECG) examinations were also performed, if necessary. Surface electroencephalography was performed on each patient to detect significant changes that might contribute to diagnosis. Computed tomography, magnetic resonance imaging and additional examinations, such as thyroid hormones, autoantibodies, and rheoencephalography, were carried out if clinically needed. Clinicians were asked to classify the types of epilepsy, epileptic syndromes, and types of seizures according to the criteria of the ILAE

The patients were asked to return for subsequent reviews at the second week, the first month, the third month, the sixth month and at successive half-year intervals from the date of initial medication. If clinical attention was necessary, more visits were scheduled between the regularly scheduled appointments. To control recall bias, each patient treated at our centres was asked to keep a medical diary with information on seizure onset, combinations with other drugs, adverse events, and hospital admissions. To control the loss of follow-up bias in the case of patients who did not appear for regular visits, follow-up data were obtained through telephone interviews or with structured questionnaire letters by mail. A patient who was lost of contact for more than one year was defined as a follow-up loss.

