**3.6 Statistical Analysis**

**3.6.1 Sample Size Calculation**

Sample size calculations were based on the primary outcome. It was assumed that the treatment failure for SRVPA and topiramate were 25% and 35% after one year, respectively. In this study, SRVPA was considered as an active comparator, there needed 415 patients for each group to achieve 90% power (β=0.1) at a 0.05 significance level to detect an equivalence hazard ratio of 1.35, assuming a dropout rate of 20% for both groups during the whole study.

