**3.6.3 Statistical Analysis Methods**

Kaplan-Meier estimates were used to describe the distribution of time to treatment failure, time to first seizure, time to 12-month remission, and time to 24-month remission. The log-rank tests were used to compare survival curves. The causes for censoring in Kaplan-Meier analysis were defined as follows: patients who were lost to follow-up, patients who died but whose death had no association with AED treatment and patients who were still receiving AED treatment at the end of this study. The censoring population was regarded as having no clinical outcome observed. Cox proportional hazard models (95% confidence interval) were used to analyse the relative risks expressed as hazard ratios (HR). In the final model, potential confounders (sex, age, type of epilepsy, seizure duration, number of previous AEDs and seizures at baseline) would be adjusted. Tolerability was assessed in the ITT population. To compare the reasons leading to treatment failure between SRVPA and topiramate, Chi-square tests and Fisher’s exact tests were used. The baseline characteristics of the two groups were compared using nonparametric tests, except the data represented as mean ± standard deviation (SD), which were analysed by using student’s t-test. All of the statistical analyses were performed with SPSS v. 13.0 software for Windows, using two-sided tests with a significance level of 0.05. No interim analysis is planned for this study.

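### Reasons for treatment failure are compared by crude chi-square/Fisher tests that ignore follow-up time, competing reasons and confounding, so two drugs with the same adverse-event failure hazard can be declared different more often than 5% of the time

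*Protocol*

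**What the plan says.** Protocol section 3.6.3 sets the test: "To compare the reasons leading to treatment failure between SRVPA and topiramate, Chi-square tests" and Fisher's exact tests. It does not say whether the denominator is all enrolled patients or only those who failed. Kaplan-Meier and log-rank are tied to four other outcomes: treatment failure from any cause, first seizure, and 12- and 24-month remission. Adjustment is tied to the Cox model: "In the final model, potential confounders (sex, age, type of epilepsy, seizure duration, number of previous AEDs and seizures at baseline) would be adjusted".

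The comparison serves a named outcome. Section 2.2 states that "the incidence of intolerable adverse events directly leading to treatment failure were also analysed". Section 2.1 puts several reasons into one composite, including "lack of efficacy combined with intolerable adverse events, poor compliance, patients’ financial hardship, or a plan of pregnancy".

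Three design features bear on the choice of test:

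- **Allocation.** Section 3.1 says that "an appropriate AED was chosen by the clinicians, taking into consideration the efficacy and adverse events of the available AEDs", together with patient characteristics and economic status.
- **Follow-up.** Section 3.6.3 censors losses, unrelated deaths and "patients who were still receiving AED treatment at the end of this study". Section 3.5 schedules reviews at "the sixth month and at successive half-year intervals from the date of initial medication".
- **Planning assumptions.** Section 3.6.1 takes one-year failure of 25% on SRVPA and 35% on topiramate, "assuming a dropout rate of 20% for both groups during the whole study".

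**The concern.** A patient who fails for one reason is no longer at risk of failing for another. If one drug loses patients sooner for lack of efficacy or cost, its patients spend less time exposed to adverse-event failure. A crude proportion then makes that drug look better tolerated. The protocol's own planning rates point this way, since topiramate is expected to fail faster.

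Two further mechanisms can act in either direction. If follow-up differs between the groups, the group watched longer accumulates more failures of every kind. If prescribers steer patients by expected adverse events, the groups differ in risk before treatment starts. The protocol recognises this confounding for the Cox model but leaves this comparison unadjusted.

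At stake is the tolerability message of a study meant to inform the choice between a traditional and a newer drug. Because the protocol states the method outright, this is a choice open to comment and not a detail left for a later document.

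**Working it through.** The protocol gives no figure for this comparison, so there is none to reproduce. The check asks how often the stated test rejects when the adverse-event failure hazard is truly identical on both drugs.

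**Inputs from the protocol**
- One-year failure of 25% and 35%. As constant hazards: −ln(0.75) = 0.288 and −ln(0.65) = 0.431 per year.
- 415 per group, two-sided 5% level.
- Visits listed to Visit 19, half-yearly after month 6. If Visit 1 is baseline, month 6 is Visit 5 and Visit 19 falls at 6 + 14 × 6 = 90 months (7.5 years). If Visit 1 is week 2, it falls at 96 months (8 years).

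**Assumptions not in the protocol**
- Adverse-event failure hazard h equal on both drugs: 0.10 per year, range 0.05 to 0.20.
- Constant hazards, except where noted.
- Equal, complete follow-up of length t, except where noted.
- All enrolled patients as denominator, except where noted.

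**Competing reasons only.** Crude incidence = (h/L) × (1 − exp(−L·t)), with L the total failure hazard.

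At t = 5 and h = 0.10:
- SRVPA: 0.10/0.288 × (1 − exp(−1.438)) = 26.5%.
- Topiramate: 0.10/0.431 × (1 − exp(−2.154)) = 20.5%.
- Difference 0.060; null standard error √(2 × 0.235 × 0.765/415) = 0.0294, so the critical difference is 1.96 × 0.0294 = 0.0577.
- Rejection = Φ((0.0599 − 0.0577)/0.0294) = 53%.

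| Follow-up (years) | SRVPA | Topiramate | Rejection, h = 0.10 | h = 0.05 | h = 0.20 |
|---|---|---|---|---|---|
| 1 | 8.7% | 8.1% | 6% | 5.5% | 7% |
| 2 | 15.2% | 13.4% | 11.5% | 8% | 21% |
| 3 | 20.1% | 16.8% | 23% | 13% | 49% |
| 5 | 26.5% | 20.5% | 53% | 27% | 93% |
| 7.5 | 30.7% | 22.3% | 79% | 43% | 99.8% |

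(The incidence columns are for h = 0.10.) In simulation at h = 0.10, a cause-specific log-rank test on the same data rejected 5.4%, 6.0% and 5.5% of the time at 1, 3 and 5 years.

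**Early, decaying adverse-event hazard.** Other-reason hazards are kept at 0.288 − 0.10 = 0.188 and 0.431 − 0.10 = 0.331; follow-up is 5 years.
- 0.30·exp(−2t): 12.8% vs 12.0%, rejection 6%.
- 0.20·exp(−2t): 8.7% vs 8.2%, rejection 6%.
- 0.25·exp(−t): 18.8% vs 16.9%, rejection 11%.

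Extending to 7.5 years changes almost nothing.

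**Variable follow-up, same in both groups (h = 0.10, constant).** Follow-up spread uniformly over 0 to 5 years gives 19%; over 0 to 7.5 years, 34%. Full 5-year follow-up with 20% loss in each group gives 46%.

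**Follow-up that differs between groups.** With every hazard identical (total 0.288, h = 0.10) but 3 years in one group and 2 in the other, the crude proportions are 20.1% and 15.2% and the test rejects 46% of the time. The simulated log-rank rejects 5.4%.

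**Confounding only.** Take adverse-event risk of 8% or 16% by stratum, the same on both drugs. If the high-risk share is 40% vs 60%, the crude risks are 11.2% and 12.8% and rejection is 11%. At 30% vs 70% they are 10.4% and 13.6%, and rejection is 29%.

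**If the denominator is failures only.** The adverse-event share is 0.10/0.288 = 34.8% vs 0.10/0.431 = 23.2%. Rejection is 52% at 1 year and 92% at 5 years.

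**When the direction could be wrong (5 years, h = 0.10 on SRVPA).** With total hazards held fixed, the crude proportions tie at a true topiramate-to-SRVPA adverse-event hazard ratio of 0.265/0.205 = 1.29. With the other-reason hazards held fixed they tie at 1.37.

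**The case against.** The strongest reply is that the large percentages come from assumptions the protocol does not make. It gives no adverse-event hazard and no study duration. The only stated planning horizon is one year, where the effect is about 6%. Dose titration makes early, fading adverse-event failures plausible, and these also bring rejection close to nominal. This stands: 53% and 79% are points in a range, not estimates for this study.

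Second, with equal and complete follow-up the crude test is a valid comparison of how many patients actually stopped for adverse events. That also stands. The fault lies in reading the result as tolerability, and such follow-up is not what the protocol describes.

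Third, nothing in the protocol says that follow-up differs between groups; the assumed 20% dropout is common to both. The unequal-follow-up and confounding figures are therefore illustrations. Nor is it settled that a lost patient counts as never having failed: that follows only if all enrolled patients are the denominator. Sections 3.6.2 and 3.6.3 point that way for secondary outcomes and tolerability, but no denominator is named for this test.

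A reader might infer that the method reverses the tolerability finding. The documents do not support that. The main calculation shows equal hazards appearing unequal. Wrong direction needs a modest true difference, and a larger one would still show the right way round.

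Finally, this is a secondary comparison; the primary outcome already has log-rank and adjusted Cox analyses. That limits the reach of the point but does not answer it.

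**Conclusion.** The point holds as a limited, worthwhile correction to a secondary analysis. The protocol fixes an unadjusted test that takes no account of time, for outcomes that compete with one another, in a non-randomised cohort with variable, censored follow-up. Two drugs with the same adverse-event failure hazard can therefore be declared different more often than the nominal 5%.

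With all enrolled patients as denominator, 415 per group, and h = 0.10 per year or an early hazard that fades quickly, rejection runs from about 6% to 53% at 5 years and 79% at 7.5 years. The low end is short follow-up or fast decay; the high figures need a constant hazard and complete follow-up. Other hazards move the 5-year figure from 27% (0.05 per year) to 93% (0.20 per year). In the competing-reasons calculation the drug that loses patients sooner for other reasons looks better tolerated. The crude result could point the wrong way only when the true hazard ratio lies between 1 and about 1.35 in the 5-year example.

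It would go too far to say that the tolerability conclusion will be reversed or that the primary analysis is compromised.

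**What to change.** In section 3.6.3, base the comparison of reasons on cause-specific Cox models in the ITT population, adjusted for the six confounders already listed there. Fit one model each for lack of efficacy, intolerable adverse events and the remaining reasons, with failures for other reasons censored at their date. Show cumulative incidence curves by reason, so that the reader also sees how many patients actually stopped for each.

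Three definitions need settling in advance:

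- **Combined reason.** Say where lack of efficacy together with intolerable adverse events counts, for example as an event in both the efficacy and the adverse-event model.
- **Poor compliance.** Report it as its own category. The protocol defines it only as stopping by the patient's own choice, which may conceal adverse events or lack of effect, so it should not be labelled a non-drug reason.
- **Denominator.** State it for the crude counts and keep those counts as description.

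The cost is a protocol wording change and a little more programming. Section 5 already records the last dose date and the reason for termination, and adjusted Cox models are already planned, so the status variables mainly need recoding. Measured confounding is then handled as in the primary analysis; unmeasured confounding remains. The primary analysis does not change.

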**3.6.4 Subgroup analysis**

Age was divided into three subgroups (2-16, >16 to 49, and >49 to 75). Seizure duration was defined as the difference between the age at the first seizure and the age at enrolment in this study and was divided into five subgroups (≤1 month, >1 month to 12 months, >12 months to 5 years, >5 years to 10 years, and ＞10 years). The number of previous AEDs was divided into four subgroups (no AEDs, one AED, two AEDs, and ≥ three AEDs). Seizures at baseline denoted the number of seizures one month before the patients’ participation in this study and were divided into four subgroups (no seizures, one seizure, two to three seizures, and ≥four seizures). Cox proportional hazard models that incorporated tests for interactions were used for all prespecified subgroup analyses.

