**3.2 Inclusion and Exclusion Criteria**

Inclusion criteria：Patients with a definite diagnosis of epilepsy, treated with SRVPA or TPM as monotherapy, between 2 to 75 years old, were enrolled in this study.

Exclusion criteria: epileptic syndromes; only acute symptomatic or non-epileptic seizures; a history of psychiatric or mood disorders; clinically significant laboratory abnormalities, including abnormal liver function, abnormal haematological system function, abnormal kidney function, abnormal endocrine system function, or heart disease; and clinician or the patient feeling that the treatment was contraindicated.

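### Seizure frequency at entry is adjusted for only through a one-month count with a single zero class; adding a 12-month rate and the date of the last seizure would be a cheap improvement

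*Protocol*

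**What the plan says.** Section 3.6.4 defines the covariate: "Seizures at baseline denoted the number of seizures one month before the" patients' participation, "divided into four subgroups (no seizures, one seizure, two to three seizures, and ≥four seizures"). Section 3.6.3 puts it in the final Cox model: "potential confounders (sex, age, type of epilepsy, seizure duration, number of previous AEDs and seizures at baseline) would be adjusted".

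No other covariate on that list measures recent frequency or time since the last seizure. The nearest in name is chronicity: "Seizure duration was defined as the difference between the age at the first seizure and the age at enrolment".

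Section 3.2 enrols "Patients with a definite diagnosis of epilepsy, treated with SRVPA or TPM as monotherapy, between 2 to 75 years old". Its exclusions, beginning with "epileptic syndromes; only acute symptomatic or non-epileptic seizures; a history of psychiatric or mood disorders", do not mention a long seizure-free interval. Section 3.6.4 provides for patients with one, two, or three or more previous drugs, so a patient controlled on an earlier drug can enter.

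Section 2.2 times remission from the start of SRVPA or topiramate treatment, and describes those who achieve it as "patients without any type of seizure for at least 12 months (or 24 months"). Under Section 3.1 the clinician and patient choose the drug, with clinical characteristics among the considerations.

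**The concern.** In a cohort without randomisation, covariate adjustment is the main protection against confounding by severity. The outcomes run over 12 and 24 months, but the severity measure looks back one month. A patient with a seizure every three months, one with two seizures eight months apart, and one already seizure-free who is changing drug for another reason will often all be scored zero. Their chances of a seizure-free year differ greatly whatever the drug does.

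Two things are at stake:

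- **Absolute results.** The remission and first-seizure curves contain some natural course as well as drug effect, whatever the balance between groups.
- **The comparison.** If the hidden mix of rates within the zero class differs between SRVPA and topiramate, the adjusted hazard ratio carries that difference.

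**Working it through.** The protocol attaches no figure to this point, so there is none to reproduce. From the protocol come the one-month window, the classes 0, 1, 2–3 and ≥4, the covariate list, the eligibility rules, and the hazard ratio of 1.35 in Section 3.6.1. Seizure rates and the strength of channelling are assumptions, because the protocol gives neither.

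**1. Who falls in the zero class.** With a constant Poisson rate r per year, P(none in 1 month) = exp(−r/12) and P(none in 12 months) = exp(−r). For r = 1 these are exp(−0.083) = 0.92 and exp(−1) = 0.37.

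| Rate per year | Scored zero, 1-month window | Seizure-free 12 months, no drug effect |
|---|---|---|
| 0.5 | 96% | 61% |
| 1 | 92% | 37% |
| 2 | 85% | 14% |
| 4 | 72% | 2% |
| 6 | 61% | 0.2% |
| 12 | 37% | about 0 |

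The one stratum thus holds patients whose chance of a seizure-free year without any drug effect runs from 61% to almost nothing. For a patient in lasting remission it is near 100%.

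**2. What an unequal mix would do.** Suppose the zero class mixes rates of 0.5 and 4 per year, 60/40 in one group and 40/60 in the other. Seizure-free at 12 months:

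- 0.6 × 0.607 + 0.4 × 0.018 = 0.371
- 0.4 × 0.607 + 0.6 × 0.018 = 0.254

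The apparent hazard ratio for first seizure is ln(0.254)/ln(0.371) = 1.38 with identical drugs. With 50/50 against 40/60 it is 1.18, and with equal mixes 1.0.

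**3. Illustrative simulation, no true drug difference.** Assumptions: lognormal rates with median 6 per year and log-SD 1.2; probability of topiramate logistic in standardised log rate; failure hazard proportional to rate^0.5; two-year follow-up. The simulation was repeated independently with a baseline failure hazard of 0.3 per year, and ranges show the spread between runs. Other planned covariates are left out.

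Hazard ratio for treatment failure:

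| Model | Odds 1.35 per SD | Odds 1.82 per SD |
|---|---|---|
| Unadjusted | 1.16–1.17 | 1.35–1.36 |
| One-month classes, as planned | 1.08–1.09 | 1.17–1.19 |
| 12-month count in the same four classes | 1.08 | 1.17–1.19 |
| One-month classes plus log 12-month count with recall error | 1.04 | 1.09 |

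The recall error assumed in the last row is multiplicative, with log-SD around 0.5 to 0.7.

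If half of the failure hazard is unrelated to seizures, the residual after the one-month classes is 1.04 at odds 1.35 and 1.07–1.08 at odds 1.82.

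For time to first seizure at odds 1.82, the figures are 1.45–1.50 unadjusted, 1.30–1.31 after the one-month classes, and 1.08–1.10 after a 12-month count in finer classes with perfect recall.

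About 55% of simulated patients fall in the zero class, and 12–14% of these had no seizure in 12 months. That is 0.55 × 0.12 to 0.55 × 0.14, or about 7–8% of all patients.

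**The case against.** **Channelling by seizure frequency is not in the protocol.** Section 3.1 names efficacy, adverse events, clinical characteristics, economic status and patient preference. It gives neither seizure frequency nor a direction. This stands: a reader might infer that frequency drives drug choice, but the text makes that plausible only. Without imbalance between groups, the comparison is not biased by this route.

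**The size rests on invented inputs.** This also stands. Treatment failure in Section 2.1 includes adverse events, poor compliance, financial hardship and planned pregnancy, which need not follow seizure rate. Epilepsy type, seizure duration and number of previous drugs are adjusted too and carry part of prognosis. For patients whose first seizure was within the last month, the one-month count already covers their whole history. Setting 1.19 alone against the design value of 1.35 would be selective.

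**Remission already has an origin.** A reader might infer that a patient entering 10 months seizure-free reaches 12-month remission two months into treatment. The description of remission does not say when the seizure-free period begins, but the preceding sentence in Section 2.2 times the outcome from the start of treatment, and Section 3.5 schedules follow-up from initial medication. The month-two reading is strained, and only a clarifying clause is needed.

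**The history may be collected anyway.** Section 3.5's first-visit list names neither the one-month count nor age at first seizure, yet Section 3.6.4 uses both. The list therefore cannot show that longer history goes unrecorded.

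**A short window limits recall error.** This is true, and Section 3.5 treats recall bias as a concern. It is a reason to keep the one-month count, but not to make it the only measure.

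**Conclusion.** The point holds as a cheap improvement. The protocol adjusts for recent seizure frequency through one coarse variable, and its zero class takes in most patients with up to about 6 seizures a year (61% or more, under assumed Poisson rates) together with those already seizure-free.

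If drug choice follows seizure frequency, the illustrative residual hazard ratio for treatment failure is about 1.04 to 1.19 with no true drug effect. It depends on the assumed channelling and on how much of failure is seizure-driven, and the other planned covariates would be expected to reduce it. The effect is larger for seizure-based outcomes, about 1.30 for first seizure under the stronger channelling. The documents do not show that the adjusted comparison is in fact biased, nor how many seizure-free patients will enter.

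**What to change.** 1. At the first-visit history, record the number of seizures in the 12 months before entry (or since onset if shorter, expressed as a rate) and the date of the last seizure.
2. Add both to the Cox models on a continuous scale, for example log(1 + rate) and time since last seizure, beside the existing one-month classes. Do not replace the one-month count, and do not put the 12-month count into the 0, 1, 2–3, ≥4 classes: in the simulation that removed almost none of the bias. The simulation tested the added count; it did not test the date of the last seizure.
3. Report 12- and 24-month remission also for patients with at least one seizure in the 12 months before entry, beside the all-patient result. Broad eligibility can stay as it is.
4. As a clarification only, state in Section 2.2 that the seizure-free period is counted from the start of SRVPA or topiramate.

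The cost is two history items and a few sentences. The 12-month count has more recall error than the one-month count, and the restricted analysis drops some patients, about 7–8% under the simulation's assumptions.
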